### Interventions

Following the baseline assessment and group allocation, the participants will receive one of the active interventions or the usual care control group. The number of sessions and duration for both interventions will be identical. A trained research assistant will administer both active interventions. A research assistant will be trained to administer the study interventions. Both interventions will consist of 12 20-min sessions which will be administered in four consecutive sessions/week for three successive weeks. The interventions described in this study adhered to the Template for Intervention Description and Replication guide.

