### Outcome measures

The assistant research fellow will collect primary outcome measures throughout the study period. All secondary outcome measures will be collected at baseline, immediately post-intervention (4th week), and 3 months post-intervention by a research assistant (RA-2) blinded to group allocation. The RA will be adequately trained to collect quantitative sensory testing procedures, electrocardiogram, and electroencephalography recordings (Table 2).

**Table 2 T2:** Secondary outcome measures.

Outcome domain and constructs (96–98)	Brief description of measurement tools	Measurement time points
Pain		
Pain severity	The brief pain inventory—short form (pain subscale) Pain severity on a 10-point scale (0 = no pain and 10 = worst pain possible) in the past 24 h, 1 week, and 4 weeks.	T_B,_ T_1m,_ T_3m_
Pain unpleasantness	In the last 2 weeks, how unpleasant has your knee pain been? ‘Not at all’, ‘slightly’, ‘moderately’, ‘very much’, and ‘extremely’.	T_B,_ T_1m,_ T_3m_
Pain bothersomeness	In the last 2 weeks, how bothersome has your knee pain been? ‘Not at all’, ‘slightly’, ‘moderately’, ‘very much’, and ‘extremely’.	T_B,_ T_1m,_ T_3m_
Intermittent and constant pain	The measure of intermittent and constant osteoarthritis pain (11 items). Each item is rated on a 5-point ordinal response scale (Not at all/No constant or intermittent knee pain, Mildly, Moderately, Severely, Extremely).	T_B,_ T_1m,_ T_3m_
Pain quality	PainDETECT questionnaire (12 items). Each symptom is rated on a 5-point ordinal response scale (1 = never to 5 = very strongly). Score classification: ≤12—nociceptive pain, 13–18—possible neuropathic pain, ≥19—likely neuropathic pain.	T_B,_ T_1m,_ T_3m_
Movement evoked pain	Pain severity during a 6-min walk distance and physical performance tasks—rated pain on NPRS on a 0–100 scale (0 = no pain, 100 = the most intense pain imaginable) scale.	T_B,_ T_1m,_ T_3m_
Flare in osteoarthritis	Flare-OA (16 items) patient-reported instrument to assess the occurrence and severity of knee OA in the past 4 weeks.	T_B,_ T_1m,_ T_3m_
Physical functioning		
Pain interference	The brief pain inventory—short form (interference subscale—nine items) evaluate the impact of pain on daily activities Rated on a 10-point scale (0 = no pain and 10 = worst pain possible).	T_B,_ T_1m,_ T_3m_

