Sleep quality and disturbances	Pittsburgh sleep quality index (19 items) assesses sleep quality over a 1-month time interval. Scored 0 (no difficulty) to 3 (severe difficulty). Total score (range 0–21). Higher scores indicate worse sleep quality.	T_B,_ T_1m,_ T_3m_
The participants’ perceptions about interventions and their impact on their health condition/pain.		
Global perceived change	Perceived change in the knee pain when compared to baseline/before training (−5 = much worse, through 0 = unchanged, to +5 = completely, recovered).	T_1m, and_ T_3m_
Acceptability of interventions	Visual analogue scales (0–10) to measure overall acceptability, burden, perceived effectiveness, ethicality, culturally acceptable, research team's trustworthiness and knowledge, and the likelihood of negative side effects of training.	T_B_
Perceived treatment satisfaction and usefulness of training	Rated on a 0–10 NRS; 0—not at all satisfied to 10—highly satisfied.	T1m, and T3m
Credibility/expectancy of the intervention	The credibility/expectancy questionnaire (5 items)	T_B_
Predictors of training		
Level of engagement with the training	Rated on a 10-point ordinal items scale, where 1 = least engaged and 10 = highly engaged.	At every session
Level of motivation	Single-item; rated on a 10-point ordinal items scale, where 1 = least motivated and 10 = highly motivated.	T_B_ and every session
Cost-and-consequences		
Costs	The osteoarthritis cost-and-consequences questionnaire will be used to measure healthcare use/expenses in the past 3 months.	T_B,_ and T_3m_
Quantitative sensory testing, physical performance assessment and physiological recordings		
	Quantitative sensory testing procedures	T_B,_ T_1m,_ T_3m_
	Resting and evoked electroencephalography.	
	Heart rate, blood pressure, and respiratory rates	
	OARSI Minimum physical performance core set	
	Short physical performance battery (SPPB) standing balance tasks.	

T_B_, at baseline; T_1m_, immediately post-intervention (4th week); T_3m_, 3 months post-intervention.

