### Safety data

The training administrator will record symptoms using the Discontinuation-Emergent Sign and Symptom (DESS) (93) checklist. The 43-item checklist includes emotional, behavioural, cognitive, and physical symptoms, and the participants will be required to compare their current status with their status prior to the training or the previous session.

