## Quantitative data analyses plan

Descriptive statistics will be derived for primary and secondary outcome measures. The sample size estimation was not determined for primary outcomes since it is a feasibility trial. However, we aim to recruit a sample (20 participants per group, 60 in total) in 1 year in a single centre to provide sufficient data for assessing adverse events, feasibility outcomes, identifying operational issues, and estimating variability estimates of clinical pain outcomes.

**In the full clinical trial**, linear mixed models will be used to examine the differences in changes in the pain and physical function between groups to determine the effectiveness of interventions against usual care based on the randomised group (i.e., using an intention-to-treat approach). Group–time interactions will be used to assess between-group differences at 1 and 3 months following the intervention, with 3 months being the primary endpoint. Potential explanatory factors (which could include age, sex, BMI, duration, baseline pain severity, and depression scores) will be adjusted in the analysis. In this feasibility study, we will still perform these analyses (with no stratification or competing exposure variables included) to assess the study protocol, focusing on the uncertainty in estimated effects, not statistical significance. The following parameters will be used to determine the sample size in the full clinical trial: standard deviations (SD) and correlations between repeated measures of outcome measures derived from the feasibility trial. The full trial will have 80% power to detect a meaningful difference in the primary outcome (i.e., pain severity at 3 months). The minimal clinically important difference for pain severity (NPRS) is 1.8 using a two-sided (0.05) significance level. An attrition rate informed by the results of this feasibility study will be incorporated.

Qualitative data analysis (72): The interviews will be audio-recorded and fully transcribed. The General Inductive Approach will guide the analysis. The qualitative findings will provide important information regarding recruitment and retention in the trial and the acceptability of interventions. The results of the qualitative study will be published separately.

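### The DESS safety checklist is worded for the two training arms only, so its symptom counts cannot be set against a concurrent usual-care level

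*Protocol article*

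**What the plan says.** Objective 2 of the protocol article is the safety of the interventions given. Under Primary outcomes, Safety data: "The training administrator will record symptoms using the Discontinuation-Emergent Sign and Symptom (DESS) (93) checklist". The checklist has 43 items covering emotional, behavioural, cognitive and physical symptoms, and participants are to "compare their current status with their status prior to the training or the previous session". The Discussion adds that symptoms are recorded weekly. It names no arm, but the paragraph is about side effects of exposure to the trainings.

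Usual-care participants are told to manage their condition as before and to come to follow-up assessments (Allocation concealment). They are offered training only once the trial is over (EEG-NF training). Their listed time is three assessments and an interview (Recruitment strategy). DESS is not among the measures in Table 2.

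Two general statements reach wider. Under Outcome measures, "The assistant research fellow will collect primary outcome measures throughout the study period". Under Quantitative data analyses plan, the 60 participants are "to provide sufficient data for assessing adverse events, feasibility outcomes, identifying operational issues", among other purposes. For the two trainings, "The number of sessions and duration for both interventions will be identical".

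**The concern.** A 43-item symptom list given to adults aged 45 to 85 with persistent knee pain will pick up some new or worse symptoms that have nothing to do with training. A randomised usual-care arm is the natural yardstick for that background, and this trial has one. But the stated comparison needs a training start or an earlier session, and usual care has neither.

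If the text is followed, DESS gives symptom counts in about 40 trainees and a fair comparison of one training with the other. Suppose both trainings provoke the same symptom, for example through sitting still with eyes closed or attending closely to the body. The two arms then look alike, and the excess cannot be told from background. The Discussion calls estimating side effects critical and presents the trial as the first source of signs and symptoms for this MMT protocol, so the missing yardstick matters for what can be concluded.

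**Working it through.** The article states no safety rate, margin or power, so there is no figure to reproduce. The check is a reading of the text followed by an illustration.

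**Does DESS, as worded, fit each arm?**

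| Element | MMT and EEG-NF | Usual care |
|---|---|---|
| Pre-training status as reference | yes | no training during the trial |
| Previous session as reference | yes, 12 sessions | no sessions |
| Listed in Table 2 at baseline, week 4 or 3 months | no | no |
| Weekly schedule (Discussion) | fits the three training weeks | no arm named, no reference point given |

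**What partly fills the gap?** Each trainee is compared with their own earlier status, which screens out stable, long-standing symptoms but not new background ones. Table 2 measures pain, mood and sleep at baseline, week 4 and 3 months. Some instruments look back over the training weeks: the flare measure is used "to assess the occurrence and severity of knee OA in the past 4 weeks", and the "Pittsburgh sleep quality index (19 items) assesses sleep quality over a 1-month time interval". These are scale scores in some of the domains that DESS covers, so the overlap is partial.

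**Illustration. Assumed: 20% of usual-care participants have a given new or worse symptom, and each training adds 20 points. Planned arm size: 20.**

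Expected counts are 8/20, 8/20 and 4/20. Wilson 95% limits: 8/20 gives 0.219 to 0.613; 4/20 gives 0.081 to 0.416; pooled 16/40 gives 0.263 to 0.554. The Newcombe limits for a difference d = p1 − p2 are

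lower = d − √[(p1 − l1)² + (u2 − p2)²], upper = d + √[(u1 − p1)² + (p2 − l2)²].

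- MMT v EEG-NF: 0 ± √(0.181² + 0.213²), that is −0.28 to 0.28.
- One training v usual care: 0.20 − √(0.181² + 0.216²) = −0.08, and 0.20 + √(0.213² + 0.119²) = 0.44.
- Both trainings pooled v usual care: 0.20 − √(0.137² + 0.216²) = −0.06, and 0.20 + √(0.154² + 0.119²) = 0.39.

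**Precision over a range of assumed rates p (the same in both groups).** Half-width = 1.96 √[p(1 − p)(1/n1 + 1/n2)], in percentage points:

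| p | 20 v 20 | 40 v 20 |
|---|---|---|
| 0.1 | 18.6 | 16.1 |
| 0.2 | 24.8 | 21.5 |
| 0.3 | 28.4 | 24.6 |
| 0.5 | 31.0 | 26.8 |

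**Secondary: the two reference points.** Assume one form a week, at sessions 4, 8 and 12, and a symptom that starts after session 1 and persists. It is scored as a change on 3 of 3 forms against pre-training status, on 1 of 3 against the previous form, and on 0 of 3 against the previous training session. The counts depend on those assumptions, but they show that the reference should be stated.

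**The case against.** The strongest reply is that the article condenses a fuller protocol, that arm-by-arm schedules often sit there, and that the weekly recording and the collection of primary outcomes over the whole study are not confined to the training arms. The listed usual-care time is 7 of about 8 hours, so brief weekly contact is not ruled out. This stands as far as it goes. But the point does not rest on silence. The article states what the participant compares with, and that comparator does not exist in usual care.

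A second reply is that Objective 2 and the Discussion concern symptoms in people exposed to training, that primary outcomes are to be summarised descriptively, and that no randomised safety contrast is promised. That is right, and it keeps the point modest: describing exposed participants is a legitimate feasibility aim.

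A third is that own-baseline comparison and Table 2 already deal with background. They do so in part. How far Table 2 overlaps with the 43 items cannot be settled, because the items are not listed.

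Two stronger readings might tempt a reader, and the document supports neither. One is that naming the training administrator excludes usual care. Under Allocation concealment, the assistant research fellow who delivers the training also meets every participant at allocation, and the same role collects primary outcomes throughout. The other is that the sample-size sentence promises DESS in all 60. It gives one total for several purposes and does not say that each uses everyone; compliance with training, for instance, can only use the training arms. Adverse events are also wider than DESS.

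**Conclusion.** The point holds as a limit on interpretation. As worded, DESS supports a description of symptoms in trainees and a randomised MMT v EEG-NF comparison with equal session number and duration. It gives no concurrent usual-care level, so background symptoms and effects common to both trainings cannot be told apart.

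The size shown rests on assumed symptom rates and full arms of 20. Under them, a shared 20-point excess appears as 0 (−28 to 28) without usual care, and as 20 points (−6 to 39, pooled) with it. Even then the interval includes zero. The gain is a descriptive estimate with stated uncertainty and does not prove attribution.

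A reader might infer that the trial cannot assess safety at all, or that the previous-session wording is an error that must go. Neither follows. Serious events have their own termination rule covering the study or an arm, and session-to-session change is useful for monitoring. That wording needs only clarifying. This is a cheap improvement worth considering, held with medium confidence because the full protocol is not shown.

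**What to change.** 1. Keep the weekly administrator-recorded DESS in both training arms for monitoring.
2. Add the same 43-item checklist to the Qualtrics questionnaires in all three arms, in the same mode, at baseline and week 4. The baseline form, completed before allocation, records symptoms present; the week-4 form rates change from baseline. Table 2 already words one item this way: "Perceived change in the knee pain when compared to baseline/before training".
3. Report the Qualtrics forms by arm, with between-arm differences and 95% CIs, as descriptive estimates only. Use only these forms for the between-arm comparison, because weekly administrator-recorded forms are not comparable with a single self-report.
4. Have the assistant research fellow, who already knows allocation, review the forms, so that the blinded assessor need not see them.
5. As a clarification, state for the weekly form which reference applies, and whether the previous session means the previous training session or the previous form.

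**Cost.** No extra visit or staff. Two forms make 2 × 43 = 86 responses per participant, or 86 × 60 = 5,160 in all. At an assumed 5 to 10 minutes a form, that is 10 to 20 minutes each. Listed time is 3 × 2 + 12 + 1 = 19 of about 20 hours in the training arms and 3 × 2 + 1 = 7 of about 8 in usual care. Assessments are capped at 2 hours, so the form belongs in the part completed at home.

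**Downsides.** It adds to a questionnaire burden that the Discussion already acknowledges. Self-report is unblinded and may carry expectation. With weekly forms over three weeks, trainees will have met the checklist three more times than controls.

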•Objective 1: To determine the feasibility (i.e., rates of participant recruitment, enrolment, training compliance, retention/dropouts) of conducting the full randomised clinical trial.•Objective 2: To examine the safety of the administered interventions.•Objective 3: To explore the participants' perceptions regarding the study procedures, including the acceptability of interventions.•Objective 4: To explore Māori perceptions of how assessment and training practices in the trial are acceptable to cultural perspectives and values, including Te Ao Māori (a Māori worldview).•Objective 5: To derive the central tendency and variability of the clinical outcome measures to inform the sample size of a full clinical trial.

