4. **Procedures:** Describe each of the procedures, activities, and/or processes used in the intervention, including any enabling or support activities.	Participants will be seated. Participants will be instructed to close their eyes, relax, and listen to the sound feedback. The participants will be instructed to minimise eye blinks, eye/head/neck movements, swallowing manoeuvres, and teeth clenching. The software programme will play a distinct tone when the brain activity of participants reaches the set threshold of infraslow magnitude at the pgACC. The RA-1 will be trained remotely by the Centre for Mindfulness (UCSD) to provide an MMT regimen in the trial. MMT involves instructing participants to focus on the sensation of each breath occurring at the tip of the nose. As a progression, the participants will be instructed to broaden their focus to the ‘full flow of the breath’, including bodily sensations. The participants will be instructed to acknowledge thoughts, feelings, and emotions as they arise without judgment and ‘simply return their attention back to the breath sensations’.
5. **Who provided** For each category of intervention provider (e.g., psychologist, nursing assistant), describe their expertise, background, and any specific training given.	A research assistant trained in delivering both interventions will administer the training.
6. **How** Describe the modes of delivery (e.g., face-to-face or by some other mechanism, such as internet or telephone) of the intervention and whether it was provided individually or in a group.	All participants will receive individual face-to-face training sessions.
7. **Where** Describe the type(s) of location(s) where the intervention occurred, including any necessary infrastructure or relevant features.	Interventions will be delivered in the School of Physiotherapy laboratory, University of Otago, Dunedin, New Zealand.
8. **When and how much** Describe the number of times the intervention was delivered and over what period of time, including the number of sessions, their schedule, and their duration, intensity, or dose.	The participants will undergo training for 12 sessions, four times a week, for three consecutive weeks. Each training session will last for a 30 min duration.

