### Baseline assessment

Written informed consent will be obtained, and the participants will be subjected to a baseline assessment to complete the questionnaires (age, sex, ethnicity, education, income, employment status, OA duration, pain severity, interference and quality, co-morbidity, psychological states, medication use, and other treatments for OA pain-management activities) (82–84) and undergo anthropometric measurements.

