Estimating a range of side effects (minor to adverse events) associated with exposure to the proposed self-regulatory training procedures is critical. We will record symptoms weekly using the Discontinuation-Emergent Sign and Symptom checklist (93). Based on the previous pilot trial, we observed no significant adverse events associated with NF training (64, 65). The brief mindfulness meditation protocol used in this trial has been thoroughly investigated in experimental acute pain conditions and people with pain. This is the first trial that will provide signs and symptoms that may be associated with this specific brief mindfulness meditation training protocol used in this trial (136).

The experienced research team trained the research assistants in administering the assessment procedures. The research team has trained the research assistant to provide training and help in troubleshooting as it arises. The trained RAs will offer training as reported in the TIDieR checklist. An expert investigator will assess the fidelity of the NF intervention administration (138). A clinical psychologist associated with the Centre for Mindfulness, University of Southern California trained the research assistant to offer MM to the participants. The MM training protocol is scripted and was adapted slightly for cultural sensitivity by the Māori investigator; hence, the fidelity assessment of delivering MM may not be essential.

The biopsychosocial outcome measures in this trial have been selected based on the recommended core outcomes for clinical trials of chronic pain (97, 98). In addition, a range of physiological measures were used alongside the clinical outcomes to explore the potential mediating mechanisms contributing to the effect of intervention (120). A future fully powered clinical trial could assess the psychological and physiological markers as mediators and moderators of treatment effects. Due to a range of outcome measures utilised in the trial, we anticipate that the participants will face a burden in terms of completing the questionnaires and undergo test procedures. However, this issue could be addressed by scheduling for some questionnaires to be completed at home and administering specific questionnaires in person (134).

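### The symptom checklist has two reference points and no rule for choosing between them, and the previous-session reference does not fit weekly recording with four sessions a week

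*Protocol article*

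**What the plan says.** Safety is listed under Primary outcomes and is Objective 2 in the Introduction: "To examine the safety of the administered interventions". The Discussion gives it weight: "Estimating a range of side effects (minor to adverse events) associated with exposure to the proposed self-regulatory training procedures is critical".

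The Safety data section sets the method: "The training administrator will record symptoms using the Discontinuation-Emergent Sign and Symptom (DESS) (93) checklist". It describes the content ("The 43-item checklist includes emotional, behavioural, cognitive, and physical symptoms") and then gives the instruction at issue: "the participants will be required to compare their current status with their status prior to the training or the previous session". It gives no response categories, no rule for choosing between the two references and no explicit frequency.

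The frequency appears in the Discussion: "We will record symptoms weekly using the Discontinuation-Emergent Sign and Symptom checklist (93". Table 1, item 8, sets the training schedule: "The participants will undergo training for 12 sessions, four times a week, for three consecutive weeks". The Interventions section also gives 12 sessions at four a week.

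The Baseline assessment section lists, among other things, "co-morbidity, psychological states, medication use, and other treatments for OA pain-management activities". It does not name the symptom checklist. Table 2 does not name it either, but that table covers secondary outcomes only.

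**The concern.** The two references answer different questions. Pre-training status shows what has emerged or worsened since the participant entered training. The previous session is a moving reference that resets each time and shows only the most recent step. With no rule for choosing, the reference can differ between participants and between sessions.

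Weekly recording makes this worse. With four sessions a week and one checklist a week, the session just before a checklist usually had no checklist of its own. A symptom that began at one of those sessions and has persisted is no worse than it was one session ago, so the comparison does not flag it.

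At stake is the safety description that the trial is meant to deliver. The instruction is given to participants at data collection. If answers are collected as change since the last session, changes at sessions without a checklist are not recorded, and later analysis cannot restore them.

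**Working it through.** The article states no harm count or rate, so there is no figure to reproduce. The check enumerates a simple course of symptoms under each reference.

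**Inputs from the document**
- 12 sessions, four a week for three weeks (Table 1, item 8; Interventions).
- Two candidate references (Safety data).
- Weekly recording (Discussion).

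**Assumptions, not in the document**
- One symptom, absent before training, begins abruptly at session *o* (1 to 12, equally weighted) and persists to session 12.
- An entry counts as emergent only if current status is worse than the reference.
- Weekly checklists fall at sessions 4, 8 and 12, or alternatively at sessions 1, 5 and 9.

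**Rules for a checklist at session *s***
- Pre-training reference: emergent if *o* ≤ *s*.
- Literal previous-session reference: the symptom must be present at *s* and absent at *s* − 1, so emergent only if *o* = *s*.

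**Checklist at every session**
- Pre-training: onset at session *o* gives 13 − *o* entries. The mean is (12 + 11 + … + 1)/12 = 78/12 = 6.5.
- Previous session: 1 entry for every onset.
- Both references catch the symptom at least once for 12 of 12 onset sessions. For example, onset at session 3 gives 10 entries against 1.

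**Weekly at sessions 4, 8 and 12**
- Pre-training: onsets 1–4 give 3 entries, 5–8 give 2 and 9–12 give 1. The mean is (4×3 + 4×2 + 4×1)/12 = 24/12 = 2.0, and 12 of 12 onsets are caught.
- Previous session: only onsets at 4, 8 and 12 are caught, so 3 of 12, with a mean of 3/12 = 0.25 entries.
- Onset at session 3 gives 3 of 3 checklists against 0 of 3, because session 4 looks the same as session 3.

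**Weekly at sessions 1, 5 and 9**
- Pre-training: onset 1 gives 3 entries, onsets 2–5 give 2, 6–9 give 1 and 10–12 give 0. The mean is (3 + 8 + 4)/12 = 1.25, and 9 of 12 are caught.
- Previous session: 3 of 12 are caught, with a mean of 0.25.

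**Weekly at sessions 4, 8 and 12, reading the reference as the previous checklist**
- 12 of 12 are caught, with 1 entry each.

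| Recording | Caught: pre-training | Caught: previous session | Mean entries: pre-training vs previous session |
|---|---|---|---|
| Every session | 12/12 | 12/12 | 6.5 vs 1.0 |
| Weekly (4, 8, 12) | 12/12 | 3/12 | 2.0 vs 0.25 |
| Weekly (1, 5, 9) | 9/12 | 3/12 | 1.25 vs 0.25 |

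Slow worsening is not in the table because the document gives no severity scale. The reasoning is qualitative: if each step between adjacent sessions is too small to be called worse, the moving reference may never flag the symptom, even when the total change since before training is plain.

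**The case against.** The strongest reply is that the wording has a natural sequential meaning: pre-training status at the first administration, the previous session afterwards. If the authors also mean the previous checklist when they write of the previous session, no abrupt onset is lost (12 of 12 caught with checklists at sessions 4, 8 and 12). The text neither confirms nor excludes this. Even so, the sequential reading keeps a moving reference for every check after the first, and the previous-checklist reading requires replacing the word on the page.

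A second reply is that the article sets no counting rule. A form that also marks symptoms as present but not worse would preserve persistence. That is fair: response categories are not given, and the entry counts above are a metric that the trial does not name. They show dependence on the reference, not the error in a planned statistic. A session-to-session comparison can also be useful for acute reactions.

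Some stronger readings are tempting but not supported:
- **That there is no baseline checklist.** The article is silent, and it is a condensed account. The baseline list is not exhaustive and Table 2 is limited to secondary outcomes. A pre-training administration is neither stated nor ruled out.
- **That persistent symptoms will be recorded as unchanged.** No such category is given for this checklist, and under the pre-training reference a persistent symptom is flagged every time.
- **That harm is under-counted ten-fold.** That ratio counts entries for one course (onset at session 3, a checklist at every session). The number ever affected is the same under both references in that case.
- **That common knee OA complaints cannot be told from emergent ones.** Sleep and mood have their own measures at baseline and at both follow-ups in Table 2.

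**Conclusion.** The point holds in a limited form. A primary safety outcome is collected against one of two references with no rule for choosing, and the previous-session reference does not fit weekly recording with four sessions a week.

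The size depends on how often the checklist is given. Under the weekly frequency in the Discussion, a literal previous-session comparison catches 3 of 12 onset sessions, against 12 of 12 with a fixed pre-training reference and checklists at sessions 4, 8 and 12 (9 of 12 with checklists at sessions 1, 5 and 9). With a checklist at every session, the number ever affected agrees for abrupt onset; entry counts differ, and slow worsening can still be missed. These figures rest on the assumed checklist timing, equally weighted onsets, full persistence and counting only entries worse than the reference.

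This is a cheap and worthwhile correction to a stated rule. It does not show that the safety data will be invalid.

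**What to change.** 1. In the Safety data section, remove the previous-session alternative, so that pre-training status is the single reference at every administration.
2. Reconcile the frequency: state in the Safety data section whether the checklist is given at every session or weekly, and make the Discussion agree. If weekly, state at which session of the week. A fixed reference cannot catch onsets after the last checklist (sessions 10 to 12 if the last one is at session 9).
3. As no pre-training administration is stated, record the 43-item checklist once before allocation, so that the reference is a record and not recall.
4. For each arm in which the checklist is used, report the number of participants with any symptom new or worse than before training, and the number still affected at the last checklist.

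The cost is one changed instruction line and one short extra form within a baseline visit planned at up to 2 h. Acute session-to-session changes would have to be noted separately if they are wanted.
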